### 2.6. Statistical Methods

The number and proportion of epilepsy cases three years after the initiation of treatment will be counted, and the 95% confidence interval of the incidence rate will be calculated using the Clopper–Pearson method. The subjects used to calculate these proportions are those in the analyzed population who have survived for up to three years following the initiation of treatment who are available for follow-up, or those who have developed epilepsy within three years of initiating treatment.

In addition, as a secondary analysis, a Kaplan–Meier curve will be drawn for the number of days until the onset of epilepsy starting from the beginning of the treatment protocol, and the incidence rate of epilepsy within the three-year study period and its 95% confidence interval will be calculated using Greenwood’s calculation formula. At that time, patients who are unable to be followed-up with or who have died will be excluded from the analysis. We will also perform a secondary analysis with mortality as a competing risk.

Regarding the above two analyses, we will also conduct separate analyses for the Glasgow Coma Scale (GCS) and the National Institutes of Health Stroke Scale (NIHSS).

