### 2.4. Sample Size

About 40 patients with a subcortical hemorrhage are admitted to the Nara Medical University hospital per year. During each registration period, which lasts for one year and six months, 54 patients (90% of 60 patients) are expected to be registered. Taking a drop-out ratio of 10% into account, approximately 48 patients will be eligible for analysis during the 3-year observation period.

Based on previous research, we know that the rate of developing epilepsy within three years after a stroke is approximately 20% [9,10,11]. If the incidence of post-stroke epilepsy can be suppressed to less than 10%, or to a maximum of 4 out of 48 cases, by the prophylactic administration of perampanel, the upper limit of the 95% confidence interval will be less than 20%, suggesting a certain level of effectiveness.

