### 3.4. Outcomes

The primary endpoint will be the percentage of patients who develop epilepsy within the first three years after the initiation of the treatment protocol. According to the International League Against Epilepsy, the definition of epilepsy, with a high likelihood of a persistently lowered seizure threshold and therefore a high risk of recurrence of events such as a stroke, is the occurrence of at least one epileptic seizure [10]. The secondary endpoints will be all-cause mortality within three years after the initiation of the treatment protocol and the occurrence of another stroke (cerebral infarction, cerebral hemorrhage, subarachnoid hemorrhage) within three years of starting the treatment protocol (regardless of whether this is a new stroke or a recurrence).

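### The primary denominator depends on the outcome: every seizure case is counted, but patients who die or are lost seizure-free before three years are dropped

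*Protocol article*

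**What the plan says.** Section 3.4 of the protocol article defines the primary endpoint as "the percentage of patients who develop epilepsy within the first three years after the initiation of the treatment protocol", with no restriction to survivors.

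Section 2.6 then narrows the denominator, which has two parts. The first part is "those in the analyzed population who have survived for up to three years following the initiation of treatment who are available for follow-up". The second part brings in the patients with an event, whatever became of them afterwards: "or those who have developed epilepsy within three years of initiating treatment". The first part has to mean alive and followed through to three years, since otherwise the second part would add nobody. On the interval, "the 95% confidence interval of the incidence rate will be calculated using the Clopper–Pearson method".

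Two secondary analyses follow. In the Kaplan–Meier analysis, "patients who are unable to be followed-up with or who have died will be excluded from the analysis". The other is a single sentence: "We will also perform a secondary analysis with mortality as a competing risk".

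Section 2.4 sets the size and the criterion. It says that "54 patients (90% of 60 patients) are expected to be registered". The allowance for attrition comes next in that section: "Taking a drop-out ratio of 10% into account, approximately 48 patients will be eligible for analysis during the 3-year observation period". At most 4 events in 48 patients should put the upper 95% limit below a historical three-year rate of about 20%.

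**The concern.** Whether a patient enters the primary denominator depends on the outcome being measured. Someone who seizes in month 2 and dies in month 6 counts in both numerator and denominator. Someone who dies in month 6 without a seizure, or is lost in month 30 without one, counts in neither. Events are kept whatever happens later; non-events are kept only if the patient is alive and followed at three years.

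The resulting proportion is not the endpoint of Section 3.4. It is neither the risk among treated patients nor the risk that would apply if nobody died or was lost. In a single-arm trial the comparison with 20% carries the whole efficacy argument, and the article does not say whether the historical rate used a similar denominator.

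Deaths and losses are to be expected. Patients are 50 to 90 years old with a cerebral haemorrhage and may be tube-fed (Section 2.2), all-cause mortality is a secondary endpoint (Section 3.4), and Section 4 acknowledges that transfers make follow-up difficult. Section 2.4 has one 10% drop-out allowance and does not say whether it includes deaths.

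**Working it through.** **1. The plan's own figures reproduce.** 40 per year × 1.5 years = 60; 0.90 × 60 = 54; 54 × 0.90 = 48.6, stated as about 48. The Clopper–Pearson upper limit is the 0.975 quantile of Beta(x + 1, n − x). For 4/48 = 8.33% it is 19.98%; for 5/48 it is 22.66%. Four is therefore the correct maximum at 48.

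**2. The same four events with different numbers of seizure-free patients removed from 54.**

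| Removed | Proportion | Upper 95% limit |
|---|---|---|
| 0 | 4/54 = 7.41% | 17.89% |
| 6 (as planned) | 4/48 = 8.33% | 19.98% |
| 7 | 4/47 = 8.51% | 20.38% |
| 12 | 4/42 = 9.52% | 22.62% |

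The planned six exclusions use up the margin. One more seizure-free death or loss moves the same four events past 20%.

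**3. Expected size of the effect.** Inputs from the article: 54 treated, 10% attrition (taken here as loss), three years, the 20% limit. Assumptions: net 3-year seizure risk fixed at 8%; constant, independent hazards; net 3-year death risk ranged over 0 to 40%, because no mortality figure is given.

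Each hazard is λ = −ln(1 − net risk)/3. With Λ the sum of the three hazards:
- seizure-free completers: F = exp(−3Λ)
- observed seizures: S = (λ_seizure/Λ)(1 − F)
- primary proportion: p = S/(S + F)

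Example at 20% death: λ_seizure = 0.02779, λ_loss = 0.03512, λ_death = 0.07438, so Λ = 0.13729. F = 0.92 × 0.90 × 0.80 = 0.6624. S = (0.02779/0.13729) × 0.3376 = 0.0683. p = 0.0683/0.7307 = 0.0935, or 9.4% before rounding of the inputs.

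For the chance of meeting the criterion, the number analysed is Binomial(54, S + F), the events given n are Binomial(n, p), and the probabilities are summed over all results with an upper limit below 20%. The last row is the cumulative incidence with death competing and no loss: λ_seizure/(λ_seizure + λ_death) × [1 − 0.92 × (1 − death risk)].

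| Net death risk | 0% | 10% | 20% | 30% | 40% |
|---|---|---|---|---|---|
| Expected number analysed, 54(S + F) | 48.8 | 44.1 | 39.5 | 34.8 | 30.1 |
| Expected primary proportion | 8.4% | 8.8% | 9.4% | 10.0% | 10.8% |
| Probability that upper limit < 20% | 56% | 45% | 35% | 25% | 17% |
| Cumulative incidence, all treated | 8.0% | 7.6% | 7.2% | 6.7% | 6.3% |

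The 0% column matches the plan's 48.6 analysed. The falling probability reflects both the raised proportion and the smaller denominator.

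**4. Direction.** Removing a seizure-free death takes away a known non-event, so for deaths the proportion always exceeds the cumulative incidence in treated patients. A lost patient's later status is unknown. If loss is unrelated to seizure, the direction is again upward; if lost patients have unrecorded seizures, the proportion could be too low.

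**The case against.** The best defence is that the rule is openly pre-specified, agrees with the 48 in Section 2.4, and errs against perampanel where deaths are concerned, so deaths cannot create a false claim of benefit. The article claims only limited evidence, and a competing-risk analysis is already planned. If the 10% drop-out already covers deaths, the 0% column applies and the effect is small: 8% becomes 8.4%.

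Much of this stands and limits the severity. It does not remove the point. The competing-risk analysis is secondary and the 20% criterion is not tied to it. The Kaplan–Meier analysis is no backstop, because it excludes deaths and losses instead of censoring them.

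A reader might infer three stronger things that the documents do not support:
- That the reported incidence is bound to be inflated. This is certain for deaths only.
- That the distortion is much larger. Holding the crude incidence at 8% while seizure-free death rises to 40% gives proportions up to 14.0% and a probability near 7%, but it forces the net seizure risk up to 10.3%. Part of that rise is a higher seizure hazard and not the denominator.
- That the remedy would restore the chance of success to about 60%. That figure comes from counting lost patients among the 54 as seizure-free, which is not the estimator proposed here.

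**Conclusion.** The point holds as a should-fix weakness of the primary analysis. Outcome-dependent entry to the denominator is explicit in Section 2.6, departs from the endpoint in Section 3.4, and meets a criterion that fails at one exclusion beyond the planned six.

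The expected sizes rest on an assumed 8% net seizure risk, 10% loss, constant independent hazards and a mortality range that is not from the documents. Without deaths the effect is slight; at 20% net death risk the expected primary proportion is 9.4% against a cumulative incidence of 7.2%. For deaths the error is conservative against 20%, so the danger is a missed effect and a comparison that is hard to interpret, not a spurious success. The sample-size arithmetic is correct as it stands.

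**What to change.** Make the primary estimate the 3-year cumulative incidence of epilepsy in all treated patients (Aalen–Johansen), with death as a competing event and losses censored at last contact. This promotes an analysis already planned and uses information from the 90-day contacts.

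The following should go with it:
- Name the 95% interval method and restate the Section 2.4 criterion for that interval.
- State whether the 20% benchmark treats death in the same way. If it does not, compare like with like, for example by Kaplan–Meier with deaths and losses censored and not excluded.
- Keep the completer proportion with Clopper–Pearson as a sensitivity analysis.
- Add a sensitivity analysis for losses, since their direction of bias is unknown.

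No new data are needed, but the cost is more than wording. The interval is no longer exact binomial, so the 4/48 justification must be reworked, and the chance of success under the new estimator has not been calculated here. The competing-risk estimate also falls as mortality rises, so against a benchmark on another basis it would be anti-conservative. The benchmark therefore has to be settled together with the estimator.

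### The secondary Kaplan–Meier analysis excludes patients who die or are lost instead of censoring them, so its three-year estimate only repeats the primary completer proportion

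*Protocol article*

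**What the plan says.** All of this stands in section 2.6 (Statistical Methods) of the protocol article.

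- **Primary analysis.** A crude proportion at three years, for which "the 95% confidence interval of the incidence rate will be calculated using the Clopper–Pearson method". The denominator takes in "those in the analyzed population who have survived for up to three years following the initiation of treatment who are available for follow-up". A second group is then added to the same denominator: "or those who have developed epilepsy within three years of initiating treatment". Epilepsy cases are therefore kept whatever happens to them later. Event-free patients who die or are lost are not counted.
- **Secondary analysis.** Here "a Kaplan–Meier curve will be drawn for the number of days until the onset of epilepsy starting from the beginning of the treatment protocol", and for the three-year rate "its 95% confidence interval will be calculated using Greenwood’s calculation formula".
- **Handling of deaths and losses in that step.** "At that time, patients who are unable to be followed-up with or who have died will be excluded from the analysis". The sentence has no exception for patients who had already developed epilepsy.
- **Further analysis.** "We will also perform a secondary analysis with mortality as a competing risk". The set of patients for it is not described.

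**The concern.** A Kaplan–Meier estimate is useful because it counts the time at risk of patients whose follow-up stops early. Removing exactly those patients takes that use away. It also makes membership of the risk set on day 1 depend on being alive and reachable at the end, so the earlier part of the curve is affected too.

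Two things are at stake. First, the secondary three-year estimate would look like a second result but would be the primary number again. It could not show how sensitive the finding is to early death or loss. Second, the sentence can be read in two ways, and the direction of the error differs between them. An analyst would have to choose after seeing who died.

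This is a stated rule, not a detail left to a later analysis plan.

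**Working it through.** **Inputs from section 2.4.** "54 patients (90% of 60 patients) are expected to be registered", 10% drop-out, about 48 analysable, and a target of at most 4 cases in 48 judged against 20%.

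**The plan's own figures reproduce.** 60 × 0.90 = 54, and 54 × 0.90 = 48.6, taken as 48. For 4/48 = 8.33%, the two-sided 95% Clopper–Pearson interval is 2.32% to 19.98%, below 20% as stated.

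**Step 1: the algebra, with epilepsy cases kept.** Let n patients remain, d of them with epilepsy and n − d complete and event-free. Nobody is censored before three years, so each risk set is the previous one less the events.

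- Survival: S = [(n−1)/n] × [(n−2)/(n−1)] × … = (n−d)/n, so 1 − S = d/n. This is the primary proportion.
- Greenwood: the sum of dᵢ/[nᵢ(nᵢ−dᵢ)] telescopes to 1/(n−d) − 1/n = d/[n(n−d)]. The variance is [(n−d)/n]² × d/[n(n−d)] = d(n−d)/n³ = p(1−p)/n with p = d/n. This is the binomial variance.

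The interval still differs from the primary one because its method differs. At 4/48 an untransformed Greenwood interval is 8.33% ± 1.96 × 3.99%, about 0.5% to 16.2%.

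**Step 2: size, with cases kept.** Assumed: 54 enrolled, 4 epilepsy cases with onset near days 100, 300, 500 and 800, and k event-free deaths or losses evenly spaced from day 30 to day 1050. Everyone else is complete to day 1080, the last visit in Table 1.

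| k | Exclusion: 4/(54−k) (SE) | Risk sets when censored | Censored Kaplan–Meier (SE) |
|---|---|---|---|
| 6 | 4/48 = 8.33% (3.99%) | 53, 51, 49, 47 | 7.78% (3.74%) |
| 12 | 4/42 = 9.52% (4.53%) | 53, 50, 46, 42 | 8.18% (3.93%) |
| 18 | 4/36 = 11.11% (5.24%) | 52, 48, 44, 38 | 8.62% (4.15%) |

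First row, censored: 1 − (52/53)(50/51)(48/49)(46/47) = 7.78%.

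The censored value depends on when onsets fall. With onsets near days 135, 405, 675 and 945:

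- k = 6, risk sets 53, 51, 48, 46: 7.86%.
- k = 12, risk sets 52, 48, 45, 41: 8.39%.
- k = 18, risk sets 52, 46, 41, 35: 9.07%.

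The cumulative incidence with death as a competing event is 4/54 = 7.4% if all k are deaths. If half are deaths, it is 7.6%, 7.8% and 8.0% for k = 6, 12 and 18.

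**Step 3: direction, with cases kept.** Assume constant independent hazards, a net three-year epilepsy risk of 20% and a death-or-loss risk of 20%. The two hazards are equal, so the share with epilepsy first is 0.5 × (1 − 0.8 × 0.8) = 18.0%. Complete and event-free is 0.8 × 0.8 = 64.0%. Exclusion gives 0.18/(0.18 + 0.64) = 0.2195, against a net risk of 20% (the target of the censored estimate) and a cumulative incidence of 18.0%. The error is upward.

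**Step 4: the literal reading.** Suppose one of the 4 epilepsy cases later dies and is removed too. With k = 6 the estimate is 3/47 = 6.4%, below the 7.8% from censoring. With k = 12 it is 3/41 = 7.3% against 8.2%. This downward pull is not automatic. In the step 3 model, where later death or loss is unrelated to epilepsy, the literal rule averages about 20.0%, the net risk. It falls below that when patients with epilepsy are more likely to die or be lost afterwards. Under this reading the estimate need not equal the primary one.

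**The case against.** **The wording may be loose.** The authors may have meant censoring. That is possible, but the text does not say so. The primary denominator in the same section does leave such patients out, so a reader has no reason to take the word otherwise.

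**It is one secondary analysis in a small single-arm study.** This stands. The primary proportion, its exact interval and the sample-size figures do not depend on the sentence. The curve would also still show when the retained onsets occur, so it is not empty; only its three-year estimate is redundant.

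**Death is handled elsewhere.** A reader might infer that the exclusion contradicts the competing-risk analysis or makes it impossible. The documents do not support that. The exclusion is tied by its opening words to the Kaplan–Meier step, the competing-risk analysis is announced separately as an addition, and nothing carries the exclusion into it. What stands is narrower: that analysis must keep deaths, and the article does not define its set.

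**The size is modest at planned attrition.** This also stands. At about 10% drop-out the gap is roughly half a point. A reader might project several points by assuming heavy mortality. The eligible age range reaches 90, and section 4 admits that follow-up is difficult, so higher attrition is plausible. No death rate is given, however, so such gaps are scenarios.

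**It does not flatter the drug.** With cases kept, this is correct. Only the literal reading can pull the estimate down.

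**Conclusion.** Wrong as written, and should be fixed. With epilepsy cases kept, the three-year Kaplan–Meier estimate and Greenwood standard error reduce exactly to the completer proportion and its binomial standard error, whatever the numbers. The gap to a censored estimate does depend on assumptions (54 enrolled, 4 events, deaths or losses evenly spread). It is about 0.5 points at 6 deaths or losses, 1.1 to 1.3 at 12 and 2.0 to 2.5 at 18, upward in each case, over the two onset patterns tried. Under the literal reading real events are deleted and the error can go downward. The planned competing-risk analysis is not contradicted, but its set needs stating. The selection in the primary denominator is a separate matter and is not counted here.

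**What to change.** Replace the exclusion sentence in section 2.6 with text to this effect:

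*All patients in the analysed population are included. In the Kaplan–Meier analysis, patients lost to follow-up are censored at last contact and deaths before epilepsy are censored at death. In the competing-risk analysis, death before epilepsy is the competing event and losses are censored at last contact. Epilepsy followed by death or loss counts as an event.*

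The wording is limited to the analysed population so that it does not override the withdrawal rules in section 2.3.

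The cost is a few sentences, submitted for review as section 3.5.3 requires. No new data are needed: survival and seizures are already checked about every 90 days (sections 2.5 and 3.3).

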### 2.7. Monitoring

To improve the accuracy of data collection, a committee of staff who are not involved in this study will monitor the data gathered from the first patient at specified time points. The committee will deliver the results to the principal investigator. No interim analyses have been planned. We define adverse events as detrimental effects on a patient’s health due to the administration of a drug. The investigators will report to the Data and Safety Monitoring Board (DSMB) and the Minister of Health, Labour, and Welfare within the established submission period if a serious adverse event occurs. We did not establish a coordinating center or trial steering committee because this trial will be conducted at a single center. We organized the DSMB according to Japan’s Clinical Trials Act (Act No. 16 of 14 April 2017). The DSMB’s members are independent of the investigators and have experience in evaluating clinical trials. The DSMB will deliberate on the directions and continuation of this trial if unpredicted serious adverse events occur. This study will not be audited. However, an audit will be considered if the monitoring reveals serious violations of relevant laws and regulations or deviations from the protocol.

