## Abstract

Background: Post-stroke epilepsy can reduce patients’ abilities to carry out various activities of daily living. Despite their importance in preventing the onset of post-stroke epilepsy, the prophylactic administration of antiepileptic drugs is controversial due to a lack of high-level clinical research. In this study, we initiated a prospective interventional study of prophylactic antiepileptic drug administration in patients with a subcortical hemorrhage, who are at the highest risk of developing epilepsy after experiencing a stroke. Methods: The study was conducted in a single-center setting and was a single-arm study with no control group; the case entry period started in November 2023 and is due to end in March 2025. Only cases with a subcortical hemorrhage will be included. The treatment regimen used in this study is 2 mg of perampanel per day. Perampanel will be administered for one year, followed by two years of follow-up, for a total study period of three years. The primary endpoint will be the development of epilepsy. Results: Perampanel administration is expected to reduce the incidence of post-stroke epilepsy in comparison to the results of previous reports on the use of alternative treatments. Conclusions: The results of this study will provide new insights into the prevention of post-stroke epilepsy. The relatively small size of this study makes it difficult to provide strong evidence of the efficacy of perampanel, but it may serve as a basis for larger clinical trials.

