### 2.5. Data Collection and Management

The results will be collected by the investigators or outcome assessors using a case report form (CRF). The investigator will evaluate patients’ eligibility using routine blood and image examinations. An investigator will ask the participants or proxies about their medication status, the occurrence of epileptic seizures or a stroke, their survival status, and the occurrence of other adverse events every three months by telephone after the initiation of the treatment protocol. Epileptic seizures are defined as the acute onset of tonic or clonic motor convulsions, absence seizures leading to an attenuation of consciousness or a loss of consciousness, automatism, sensory abnormalities, and autonomic neurological symptoms. The investigator will determine whether the symptoms are indicative of epileptic seizures based on the information provided by the patient or a witness. The diagnosis of post-stroke epilepsy is based on the occurrence of a single seizure. Typically, epilepsy is diagnosed based on the occurrence of two or more seizures that occur at a certain interval. However, as reported by Fisher et al., post-stroke epilepsy can be diagnosed based on a single seizure due to its high recurrence rate [12]. This study also adopted this diagnostic criterion.

All information in the study protocol will be collected by the investigator during the study period and recorded on CRFs that will be stored at the Nara Medical University data center.

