### 3.3. Participant Timeline

All outcomes will be evaluated, and data will be collected according to the participant’s timeline (Table 1). Neurological findings, blood tests, and imaging studies will be performed when a patient enters the study to confirm whether or not the patient is eligible to participate in the study. After the completion of the drug administration protocol, the patients will be followed-up with for another 2 years. Patient status should be checked every 90 days (allowed within ± 10 days) during the administration and follow-up periods and it will be confirmed through a telephone interview or outpatient visit. During the follow-up, patients will be checked for survival, the occurrence of seizures, the occurrence of another stroke, and adverse events.

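### Section 2.7 defines an adverse event as harm caused by a drug, which conflicts with Sections 2.5 and 3.3 and, read literally, narrows serious-event reporting to the DSMB

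*Protocol article*

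**What the plan says.** The only definition of an adverse event in the protocol article is in Section 2.7 (Monitoring): "We define adverse events as detrimental effects on a patient’s health due to the administration of a drug". The next sentence uses the same term to trigger a report to the DSMB and the Minister, "within the established submission period if a serious adverse event occurs". Later in that section, the DSMB's deliberation on continuing the trial also depends on serious adverse events.

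The sections on data collection are worded differently. Section 2.5 has an investigator ask about medication and "the occurrence of epileptic seizures or a stroke, their survival status, and the occurrence of other adverse events every three months by telephone". Section 3.3 covers the two years after drug administration ends: "During the follow-up, patients will be checked for survival, the occurrence of seizures, the occurrence of another stroke, and adverse events". Neither sets a condition on cause.

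Some harms are endpoints in their own right. Section 3.4 states: "The secondary endpoints will be all-cause mortality within three years after the initiation of the treatment protocol". It adds any further stroke, "regardless of whether this is a new stroke or a recurrence". According to the Abstract, this "was a single-arm study with no control group", and Section 3.2 describes the use of perampanel as off-label.

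**The concern.** An adverse event is normally any untoward occurrence after treatment starts, and whether the drug caused it is a separate judgement made afterwards. Section 2.7 merges the two, so an occurrence must already be judged drug-caused before it counts.

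This trial is badly placed to tolerate that. The patients are 50 to 90 years old with a recent hemorrhage, and a fall, drowsiness or a change in behaviour is easily put down to the stroke. With a control arm, an excess of such events might show even if each one had been judged unrelated. Here nothing plays that part. Two things are at stake: a usable harm rate to set against any preventive benefit, in a study meant to inform larger trials, and the completeness of the serious events that the DSMB sees.

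**Working it through.** The plan gives no figure on this point, so the main check compares its statements.

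**1. Section 2.7 against Section 2.5.** Section 2.7 requires causation by a drug. Section 2.5 lists seizures, stroke and survival and then asks about other adverse events. The word other places the listed items among the adverse events, and they are collected whatever their cause. Both usages cannot hold.

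**2. Section 2.7 against Section 3.3 and Table 1.** Of the 12 scheduled contacts in Table 1, 4 (days 90 to 360) fall in the intervention period and 8 (days 450 to 1080) in the follow-up. Section 3.3 asks for adverse events in that follow-up. Under Section 2.7 they would count only if due to a drug, although the study drug has stopped. The definition says a drug, not the study drug, so harm from another medicine would still qualify. The mismatch is one of scope; the category is not empty.

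**3. What is captured in any case.**
- Deaths: an all-cause endpoint (Section 3.4), with survival checked at each contact.
- Further strokes: an endpoint with no condition on cause (Section 3.4).
- Seizures: the basis of the primary endpoint, asked about directly (Sections 2.5 and 3.3).

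**4. What is left exposed.** Non-fatal events other than stroke and seizure, and the serious-event report, which inherits the causal condition from the sentence before it.

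**5. Illustration of size.** The event risk and the attributed share are assumptions; the documents give neither. Expected registrations are 40 per year × 1.5 years = 60, and 60 × 0.90 = 54 (Section 2.4). Let p be the true risk of a given type of event and s the share attributed to a drug and so recorded. Then the recorded rate is p × s, the expected number recorded is 54 × p × s, and the chance of recording at least one is 1 − (1 − p × s)^54.

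| True risk p | All recorded | s = 75% | s = 50% | s = 25% |
|---|---|---|---|---|
| 5% | 2.70 | 2.03 | 1.35 | 0.68 |
| 10% | 5.40 | 4.05 | 2.70 | 1.35 |
| 20% | 10.80 | 8.10 | 5.40 | 2.70 |

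(Expected number of patients with a recorded event.)

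At p = 5%, the chance of recording at least one event is 93.7% with full recording, and 87.3%, 74.5% or 49.3% at s = 75%, 50% or 25%. At p = 20% it stays at 93.7% or above throughout. There the loss is in the rate; the type of event would still be noticed.

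**The case against.** A reader might infer from Section 2.7 that only events the investigator blames on a drug are recorded. The article does not say so. It sets no attribution filter on the case report form and does not say who judges causality. The three-monthly question in Section 2.5 carries no causal condition, and Section 2.5 also says that all information in the study protocol goes onto the form. Deaths, strokes and seizures are collected regardless. Section 2.3 lists worsening complications as a discontinuation criterion without reference to cause, which again suggests a wider intent than Section 2.7 expresses. A site following Section 2.5 might well record everything.

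It is equally tempting to say that almost nothing could count in the two years after the study drug ends. The wording a drug does not support that.

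The size rests wholly on assumed rates, and no adverse-event rate is among the endpoints in Section 3.4 or the analyses in Section 2.6. The layout of the form and the safety tables are matters that an article may leave to the full protocol, so their absence is no fault.

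All of this stands, and it limits the point to the definition and what depends on it. It does not clear the definition. That sentence is stated, not omitted. It is the only definition in the article, and the serious-event rule depends on it. A site that records more widely does so in spite of Section 2.7.

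**Conclusion.** The point holds in a limited form. Section 2.7 defines an adverse reaction under the name of adverse event and is inconsistent with Sections 2.5 and 3.3. Followed to the letter, it allows non-fatal events other than stroke and seizure to go unrecorded when they are ascribed to the stroke, and it keeps serious events judged unrelated from the DSMB. The lack of a control group makes this matter more than it otherwise would.

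The primary endpoint and both secondary endpoints are unaffected. Loss of data is a risk created by the wording; the documents do not show that it will happen. If the definition were applied strictly, the recorded rate would be the attributed share of the true rate. The documents give neither quantity, so no single figure should be quoted as the expected under-recording. The point merits correction because an event that was never recorded cannot be reassessed for relatedness later.

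**What to change.** Reconcile Sections 2.5, 2.7 and 3.3 under one definition: an adverse event is any untoward medical occurrence after the first dose, whatever its cause. Record seriousness and relatedness to the study drug as separate items, and state who makes the relatedness judgement. Apply the serious-event report to the DSMB to all serious events, with relatedness noted on the report. Report all-cause and drug-related rates side by side.

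The change replaces one definition and separates two items on the form, using the 90-day contacts already planned. It leaves treatment, visits and endpoint analyses as they are. The cost is more events to record and, for the serious ones, more reports for the DSMB to read. In this population many will be consequences of the stroke.
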